#### Adverse events

Adverse event data will document the occurrence, duration, and severity of adverse reactions (symptoms and signs), and how the event was resolved (or not) during the treatment. For acupuncture, common and expected adverse events include local hematomas; needle breakage; needle retention after treatment; fainting; unbearable prickling, severe pain, or discomfort persisting for more than 1 h after acupuncture; local infections; abscesses; and deterioration of blood laboratory parameters. All participants will receive routine blood, urine, and stool tests; and electrocardiogram, liver function (alanine transaminase and aspartate transaminase), and kidney function tests (serum creatinine and blood urea nitrogen). These tests will be performed twice after randomization and at the end of the 4-week treatment period. The researchers will report all adverse events to the Research Ethics Committee of Beijing Hospital of Traditional Chinese Medicine Affiliated to Capital Medical University and treat the participants with relevant conventional therapy or hospitalization if necessary (the participant’s allocated intervention will be revealed). Researchers will evaluate the relationship between adverse events and the interventions. The number of adverse events will be recorded and divided by the sample size of each group to calculate the incidence.

The enrolment schedule, treatment, and outcome measures are presented in Fig. 2.

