**Methods/design:**

This is a prospective randomized controlled pilot trial design in which 120 eligible patients will be randomly allocated to one of three groups. The acupuncture group (*n* = 40) will receive acupuncture and routine care, the medication group (*n* = 40) will receive mosapride citrate and routine care, and the control group (*n* = 40) will receive only routine care for ischemic stroke. Patients will be recruited 2 weeks to 6 months after stroke onset and will receive the intervention continuously over 4 weeks, with a follow-up period of 4 additional weeks. Adverse events will be recorded to assess the safety and tolerability of acupuncture for constipation after an ischemic stroke. The primary outcome will be the change in the weekly mean number of complete spontaneous bowel movements. Secondary outcomes will include any change in the weekly mean number of spontaneous bowel movements, mean stool consistency scores, mean straining scores during defecation, and frequency of laxative use. All outcome measures will be assessed at inception, after the intervention (4 weeks), and at the follow-up (8 weeks).

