## Methods/design

### Study design

This is a prospective parallel-arm randomized controlled pilot trial comparing acupuncture with a pharmacological intervention (mosapride citrate) and usual care (control group). We will recruit patients who have sustained an ischemic stroke and present with constipation, according to predefined inclusion and exclusion criteria, between January 2017 and September 2019. Participants will be randomly allocated to one of three groups and will receive continuous treatment for 4 weeks. Repeat assessments will take place after treatment and later, at 8 weeks after inception. All participants will be asked to keep a defecation diary including weekly number of complete spontaneous bowel movements (CSBMs), SBMs, stool consistency, defecation difficulty, and laxative use and dosage, beginning at baseline during the 8-week assessment period. All outcomes will be assessed at baseline, and at 4- and 8-weeks after randomization, according to the defecation diary (Fig. 1).

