### Blinding

Data managers (including the telephone interviewer during the follow-up period) and statisticians will be blinded to participant group assignment. Therapists, data managers, and statisticians will not be allowed to communicate with others about the participants’ allocation.

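### Adverse event documentation carries a treatment-period limit, so late-onset events and the outcome of events open at week 4 may go unrecorded although patients are followed to week 8

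*Protocol article*

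**What the plan says.** The Abstract of the protocol article states the aim without a time limit: "Adverse events will be recorded to assess the safety and tolerability of acupuncture for constipation after an ischemic stroke". The Discussion again promises preliminary data on safety and tolerability.

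The Adverse events section opens with "Adverse event data will document the occurrence, duration, and severity of adverse reactions (symptoms and signs" and, in the same sentence, adds "how the event was resolved (or not) during the treatment". It then lists the events expected with acupuncture, ending with "local infections; abscesses; and deterioration of blood laboratory parameters". Of the laboratory tests and electrocardiogram it says: "These tests will be performed twice after randomization and at the end of the 4-week treatment period". It also says "The researchers will report all adverse events to the Research Ethics Committee", and defines incidence as the number of events divided by group size, with no period named.

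Under Study design, participants "will receive continuous treatment for 4 weeks" and are assessed again at week 8. The Follow-up section describes weeks 5 to 8 (routine care, emergency laxatives, no acupuncture or mosapride) and does not mention adverse events. The Blinding section shows that patients are contacted in that period, since it refers to data managers "including the telephone interviewer during the follow-up period".

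**The concern.** The efficacy outcomes are defined over both the treatment and the follow-up period, and the text names both. The safety text names only the treatment period. A site following it literally could stop recording at the last session or last tablet.

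Two kinds of event would then be lost or cut short. The first is an event that starts after week 4, such as an infection at a needle site from one of the last sessions, or an event after mosapride is stopped. The second is an event that starts during treatment and is still open at week 4, whose duration and outcome would be incomplete. The incidence formula gives no period, so two readers could count different events from the same trial and both claim to have followed the plan.

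**Working it through.** The article gives no figure to reproduce on this point. The check is a comparison of the stated windows, with simple arithmetic.

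**Inputs.**
- Treatment: 4 weeks (Study design).
- Follow-up after treatment: 4 weeks, without acupuncture or mosapride (Follow-up).
- Acupuncture sessions: 5 a week in weeks 1-2 and 3 a week in weeks 3-4, so 5 + 5 + 3 + 3 = 16, with 3 in the last week (Acupuncture group).
- Last dated safety tests: end of week 4 (Adverse events).
- Group size: 40 (Sample size).

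**Reading A: the time phrase governs the whole sentence.**
- Share of observed time in which onset is documented: 4 / (4 + 4) = 0.50.
- Share of the exposure period: 4 / 4 = 1.00.

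**Reading B: the time phrase governs only resolution.**
- Onset has no stated limit and could be documented for 8 / 8 weeks.
- Resolution is recorded only up to week 4. Take treatment to end on day 28 and follow-up on day 56 (4 × 7 and 8 × 7). An event starting in the last treatment week, days 22 to 28, has between 28 − 28 = 0 and 28 − 22 = 6 days in which its resolution can be recorded. With follow-up to week 8 it would have between 56 − 28 = 28 and 56 − 22 = 34 days.

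**With recording stated to week 8.** Onset is covered for 8 / 8 weeks, and open events are followed for up to 4 weeks longer. The incidence denominator stays at 40 per group.

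**Side by side.** The primary outcome and the laxative-use outcome each name both the treatment and the follow-up period. The adverse event sentence names treatment only. The Follow-up section adds nothing on adverse events. The duty to report all adverse events to the ethics committee has no time limit, but it is a duty to notify and not a schedule for asking patients. No text shown provides for collecting adverse events in weeks 5 to 8.

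**The case against.** The strongest answer is that the sentence sets no collection window at all. Its time phrase directly follows the clause on resolution, while occurrence, duration and severity carry no limit of their own. The reporting duty and the safety aim are also open-ended. That is a fair reading, and it means that non-recording of follow-up events is not established. It does not clear the text, because on this reading the outcome of events open at week 4 is still limited to treatment. The words allowing an event to be noted as unresolved record its status at that point, not what became of it.

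Second, the section sends the reader to Fig. 2 for the schedule, and the figure is not shown. It may include adverse events to week 8, and its absence cannot be held against the plan. A condensed article may also leave case report form detail to the full protocol. This stands as a caution. The point here is a limit that the article does state, not a detail it leaves out.

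Third, no study treatment is given after week 4, so tests at the end of treatment match the end of exposure. Not repeating them at week 8 is a defensible choice and is not criticised here.

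A reader might also infer three stronger things that the documents do not support:
- **The safety question is answered for only half the follow-up.** The 50% holds only on Reading A, and the whole exposure period is covered on either reading.
- **The protocol lists delayed events and then ignores them.** Abscesses and infections are listed as expected, with nothing said about time of onset. That one could appear after a week-4 session is an assumption.
- **Acupuncture patients are asked about adverse events more often, at their 16 sessions.** No text says that they are questioned at sessions. All arms have the same safety tests and the same week-4 and week-8 assessments, and a longer window would not remove an imbalance in weeks 1-4 if there were one.

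**Conclusion.** The point holds as a stated limit that should be changed, not as a proven loss of safety data. On the broad reading, events starting in 4 of the 8 weeks are undocumented. On the narrow reading, events open at week 4 are not followed to an outcome. On both, the 4 weeks of exposure are covered, so the gap is confined to late-onset and unresolved events. The documents give no expected number of these, and none is assumed here.

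The conclusion rests on the text as shown. If Fig. 2 or the full protocol schedules adverse event collection to week 8, what remains is a mismatch in wording to be aligned. The primary efficacy analysis is unaffected. The change is worth making because safety and tolerability are a stated aim, the results are meant to inform a larger trial, and the contacts needed already exist.

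**What to change.** Amend the Adverse events section to state that:
1. adverse events are recorded in all three arms from randomisation to week 8;
2. events still open at week 4 are followed to resolution or to week 8, whichever comes first;
3. the same short set of questions is put to patients in every arm at the week-4 assessment and at the existing follow-up contacts, including the telephone interview;
4. these questions are asked after the diary data have been taken;
5. incidence is reported separately for weeks 1-4 and weeks 5-8.

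Check Fig. 2 and the full protocol, and make all three agree.

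The cost is a few questions at contacts already planned and a case report form page. More events will be recorded, most of them probably unrelated to treatment. Answers may reveal the arm to the blinded telephone interviewer; the order in item 4 limits this for the diary data at that contact but does not remove it. The change concerns data collection only and alters no treatment or clinical rule.

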### Randomization and allocation concealment

Participants will be randomly assigned to one of three groups (the acupuncture group, the medication group, or the control group) using a 1:1:1 ratio. The generation and allocation of a random sequence for group assignment will be conducted by the Research Centre of Clinical Epidemiology, which is affiliated to Peking University Third Hospital in China. Individuals involved in participant randomization will be blinded and will not participate in the recruitment and inclusion of participants. The block randomization method (block size of 6) will be adopted to generate the random sequence, using the Statistical Analysis System (V.9.1.3; SAS Institute Inc., Cary, North Carolina, USA). Opaque computer-generated sealed envelopes will be produced for the randomization and allocation. The envelopes will be numbered consecutively with a serial number on the outside and will contain the allocation information. An envelope will be opened when a participant enters the study after the baseline measurements have been taken. Participants will be allocated to one of the three groups and receive an intervention according to their group allocation. The random allocation sequence and the opaque sealed envelopes will be kept separately by two specific researchers.

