#### Sample size

Since there are no previous three-armed randomized controlled trials that investigate this topic, the present study will provide effect size data for sample size calculations of subsequent large-scale randomized controlled trials. For practical reasons, a sample size of 40 per group and a total number of 120 participants will be recruited during the entire study according to outpatient and inpatient censuses of the hospital.

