#### Acupuncture group

All the study acupuncturists will be registered practitioners of traditional Chinese medicine with at least 5 years’ clinical experience, as well as a medical education background. The acupuncture treatments and manipulations will be standardized among acupuncture practitioners through live and recorded training. Outpatients will receive treatment in clinics and inpatients will be treated in wards. If inpatients are discharged, they will receive acupuncture in clinics by the same acupuncture practitioner. Sterile needles (size 0.30 × 40 mm and 0.35 × 75 mm; Guizhou Ande Medication Appliance, Ltd., Guiyang City, Guizhou Province, China) will be used.

For the acupuncture, we will use Wang’s classical 10 acupoints formula. These acupoints have been selected and combined for gastrointestinal disease after a stroke based on the clinical experience of an accomplished Chinese acupuncturist, Leting Wang, in the 1960s [26, 27]. The 10 acupoints include CV13 (*shangwan*), CV12 (*zhongwan*), CV10 (*xiawan*), bilateral ST25 (*tianshu*), CV6 (*qihai*), bilateral PC6 (*neiguan*), and bilateral ST36 (*zusanli*). All of the acupoints will be located according to the World Health Organization Standardized Acupuncture Points Location [28]. After sterilizing the skin, needles will be slowly and vertically inserted into ST25 (*tianshu*) bilaterally, without any manipulation. Needle insertion will stop upon piercing of the muscle layer of the abdominal wall (nearly 20 to 60 mm subcutaneously). Known side effects of needle insertion include mild soreness. Other needles will be inserted to a depth of 10–25 mm to predetermined acupoints and manually manipulated by rotation to produce the characteristic sensation of *deqi*. The *deqi* sensation is also called *needle sensation*, and refers to perceived subcutaneous tension around the needle, which is felt by the acupuncture practitioner, and soreness, numbness, distension, and heaviness around the acupuncture point that is felt by the participant. Each session will last for approximately 30 min. All needles will be removed with sterile cotton balls to avoid bleeding.

Each participant will be treated once a day and will receive 16 treatment sessions in total over 4 consecutive weeks. Treatment will be conducted 5 times per week in the first 2 weeks and 3 times per week in the last 2 weeks.

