### Statistical analysis

The analysis of the primary outcome will be based on both a full analysis (intention-to-treat analysis) and per-protocol sets (per-protocol analysis). The analyses of secondary outcomes will be based on the per-protocol sets. The full analysis set refer to the participants who are randomized and receive at least one treatment session. Any missing data will be replaced by the last measured value. The per-protocol sets will be defined as the participants who receive all treatment sessions and completed the study according to the protocol.

The statistical analysis will be performed by a statistician who is blinded to participant group allocation and will not be involved in other aspects of the study. The SPSS statistical package (version 18.0, International Business Machines Corporation, China) will be used to analyze the data. All data will be kept in duplicate by specific researchers. The results of the quantitative data analyses will be presented as means ± standard deviation. The Kolmogorov–Smirnov test will be applied as the normality test for quantitative variables. The Wilcoxon test or analysis of variance (ANOVA) will be used to compare the difference between groups according to the results of the Kolmogorov–Smirnov test. The results for categorical data will be compared with the chi-squared test and presented as a percentage. The statistical significance level will be set at 0.05 (two-sided) with a 95% confidence interval.

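### Adverse event incidence is defined as events per participant, not the share of participants affected, so repeat events can inflate it and it has no 100% ceiling

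*Protocol article*

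**What the plan says.** The Adverse events section gives the formula: "The number of adverse events will be recorded and divided by the sample size of each group to calculate the incidence". It has no rule for several events in one participant, and it does not ask for the number of participants affected.

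The denominator comes from Sample size, where "a sample size of 40 per group and a total number of 120 participants will be recruited", and from Randomization and allocation concealment, where allocation is made "using a 1:1:1 ratio".

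On exposure, the Acupuncture group section says: "Each participant will be treated once a day and will receive 16 treatment sessions in total over 4 consecutive weeks". For that treatment the Adverse events section says that "common and expected adverse events include local hematomas; needle breakage; needle retention after treatment; fainting", and its list goes on to severe or prolonged pain, local infection and others.

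On testing, Statistical analysis has a general rule: "The results for categorical data will be compared with the chi-squared test and presented as a percentage". It adds: "The statistical significance level will be set at 0.05 (two-sided) with a 95% confidence interval". Neither sentence mentions adverse events.

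**The concern.** A reader of the trial report will take an incidence of adverse events, shown as a percentage, to be the share of patients harmed. The stated formula yields a different quantity: total events divided by participants. One participant with four hematomas counts the same as four participants with one hematoma each.

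The difference would not fall evenly on the arms. Acupuncture participants undergo a repeated procedure, and several of the listed events can recur from session to session. The medication and control arms have no repeated needling. The distortion would therefore fall mainly on the experimental treatment and could make it look less safe than it is.

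The abstract gives safety and tolerability as the reason for recording adverse events. The Discussion says that the trial will supply preliminary safety data, and the abstract says that its findings will inform larger trials. A misdefined incidence would carry into that planning.

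**Working it through.** The protocol states no adverse event rate, so there is no published figure to reproduce. The design figures agree with one another: 3 × 40 = 120 participants, and 5 × 2 + 3 × 2 = 16 sessions.

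**Inputs from the protocol.** 40 participants per arm; 16 acupuncture sessions per participant, so 40 × 16 = 640 participant-sessions in the acupuncture arm.

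**Assumed input.** A per-session event probability *r*, the same for everyone and independent between sessions, with at most one event per session. The range shown is 1% to 10%.

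**Formulas.**
- Protocol rule: expected events ÷ 40 = 640*r* ÷ 40 = 16*r*.
- Share of participants with at least one event: 1 − (1 − *r*)^16.

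| Assumed *r* | Expected events (640*r*) | Protocol rule (16*r*) | Participants affected |
|---|---|---|---|
| 1% | 6.4 | 16% | 14.9% |
| 2% | 12.8 | 32% | 27.6% |
| 5% | 32.0 | 80% | 56.0% |
| 6.25% | 40.0 | 100% | 64.4% |
| 8% | 51.2 | 128% | 73.7% |
| 10% | 64.0 | 160% | 81.5% |

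**Ceiling.** The ratio exceeds 100% once an arm has more than 40 events. In the acupuncture arm that is *r* > 40 ÷ 640 = 6.25%.

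**Gap.** It is 16 − 14.9 = 1.1 percentage points at 1%, 80 − 56.0 = 24.0 at 5% and 128 − 73.7 = 54.3 at 8%. If events cluster in susceptible participants, fewer people are affected for the same number of events, and the gap widens. If no participant has more than one event, events and affected participants are the same number and the gap is zero.

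**What a test on event counts would do, if one were run.** A chi-squared test treats the 40 units in each arm as independent and counted once. A simulation of three arms of 40 with identical true risk (40,000 trials per setting, two-sided 0.05) assumed that 10% to 30% of participants have an event and that each affected participant has a Poisson number of extra events. Event results use only trials in which no arm exceeded 40 events.

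| Mean extra events per affected participant | False rejection, events counted | False rejection, participants counted |
|---|---|---|
| 0 | 4.4–5.0% | 4.4–5.0% |
| 0.5 | 21–32% | 4.5–5.1% |
| 1 | 36–53% | 4.3–5.0% |
| 2 | 55–65% | 4.5–5.1% |

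Above 40 events in an arm, the no-event cell would be negative and no table can be formed. These rates illustrate the mechanism under assumed inputs; they are not properties of the written plan.

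**The case against.** The strongest objection concerns the test. A reader might infer from Statistical analysis that adverse event incidence will be compared by chi-squared, and so that the trial's safety p-values are already invalid. The protocol does not support that. Its chi-squared sentence covers categorical data in general and could refer to baseline variables; the Adverse events section plans a calculation, not a comparison between arms. The inference is plausible, because the primary and all four secondary outcomes are quantitative, but it remains an inference. A statistician who met more than 40 events in an arm would also see at once that no table can be built. This part of the objection stands, and the test consequence is only conditional.

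Second, the size depends on event rates that the protocol does not give. At 1% per session the two definitions are nearly the same, and several listed events, such as needle breakage or abscess, have a high threshold. This stands as to size. It does not remove the error in the definition, since hematomas or pain could plausibly recur.

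Third, the sentence may be loose shorthand in a condensed article, with the counting of repeat events left to a fuller document. That would answer a complaint about missing detail. Here, however, the article states a specific formula with events as the numerator, and that formula does not give the quantity it names.

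**Conclusion.** The point holds as an error of definition. Followed as written, the rule reports mean events per participant under the name of incidence. How far this misleads depends on how often events recur: not at all without repeats, negligibly at about 1% per session, and substantially from about 5% per session. Those rates, and independence between sessions, are assumptions.

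Any effect on a significance test depends on two further conditions: that adverse event counts are tested at all, and that some participants have more than one event. The primary outcome is not affected. The correction is worth making because safety is a stated purpose and the present wording is wrong for the quantity it names.

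**What to change.** Replace the sentence in the Adverse events section with a definition along these lines:

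- Incidence is the number of participants with at least one adverse event, overall and by type, divided by the number of participants in that arm who received the allocated care.
- The total number of events is reported separately, per participant in every arm and also per session in the acupuncture arm.
- Any between-group test (chi-squared, or Fisher's exact where counts are small) is based on participants, not events.

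The cost is two or three sentences. The statistical section defines only full analysis and per-protocol sets, so the denominator has to be written out as above, not cited as an existing safety set. No new data should be needed, provided that each recorded event can be traced to its participant. The protocol already documents the occurrence, duration and severity of events and has the researchers judge their relationship to the interventions. If no participant has more than one event, the reported figures do not change.
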